# Angiotensin-converting enzyme inhibitor for post-transcatheter aortic valve implantation patients: study protocol for a multicenter randomized, open-label blinded endpoint control trial

**DOI:** 10.1186/s13063-021-05411-5

**Published:** 2021-07-18

**Keywords:** Aortic stenosis, Fosinopril, Left ventricle mass, Renin-angiotensin system inhibitor, Prognosis

## Abstract

**Background:**

With the expanded utilization of transcatheter aortic valve implantation (TAVI) to younger and lower surgical risk patients with severe aortic stenosis (AS), optimal medical therapy after TAVI procedure has become the main concern. Renin-angiotensin system inhibitors (RASi) are widely utilized in the area of cardiovascular disease including heart failure and myocardial infarction and revealed the ability to reverse left ventricular (LV) remodeling. Interests have, thus, been drawn in investigating whether the prescription of RASi after the TAVI procedure can prevent or reverse cardiac remodeling and improve long-term clinical outcomes. No recommendation regarding the prescription of RASi after TAVI is proposed yet due to the lack of evidence from randomized controlled trials, especially in the Chinese population. We, therefore, designed this randomized controlled trial to explore the effect of adding fosinopril to standard care in patients who underwent a successful TAVI procedure on the LV remodeling.

**Methods:**

A total of 200 post-TAVI patients from seven academic hospitals across China will be recruited and randomized with a ratio of 1:1 to receive standard care or standard care plus fosinopril. Follow-up visits will take place at 30 days, 3 months, 6 months, 12 months, and 24 months from randomization to assess the clinical symptoms, any adverse events, cardiac function, and quality of life. Cardiac magnetic resonance will be performed at baseline and repeated at the 24-month follow-up visit to assess LV remodeling.

**Discussion:**

This study will provide evidence regarding medical therapy for AS patients who underwent TAVI and filling the gap in the Chinese population.

**Trial registration:**

Chinese Clinical Trial Registry ChiCTR2100042266. Registered on 17 January 2021

**Supplementary Information:**

The online version contains supplementary material available at 10.1186/s13063-021-05411-5.

## Administrative information

Note: the numbers in curly brackets in this protocol refer to SPIRIT checklist item numbers. The order of the items has been modified to group similar items (see http://www.equator-network.org/reporting-guidelines/spirit-2013-statement-defining-standard-protocol-items-for-clinical-trials/).

## Introduction

### Background and rationale {6a}

Aortic stenosis (AS) is the most common valvular heart disease in the elderly population [1]. With the acceleration of the Chinese population aging, the prevalence of aortic stenosis is thought to increase markedly. Surgical aortic valve replacement (SAVR) is regarded as the only effective method for patients with aortic stenosis in the past decades. However, numerous evidence have demonstrated transcatheter aortic valve implantation (TAVI) to be comparable and sometimes superior in treating patients with aortic stenosis regardless of risk stratification, in comparison with SAVR [2].

Patients with aortic stenosis typically accompany with left ventricular (LV) hypertrophy or fibrosis indicating a worse long-term clinical outcome [3]. A majority of patients continue to present left ventricular hypertrophy even after SAVR or TAVI, who had a high risk for mortality and heart failure re-admission [4]. A previous meta-analysis found that the 30-day and 1-year incidence of re-admission following TAVI was 15% and 31%, respectively, of which nearly half resulted from the cardiac cause [5]. Compared with that of SAVR, TAVI is associated with a high risk for paravalvular leakage, even in patients with a new-generation transcatheter heart valve. The persistent left ventricular hypertrophy and new-onset paravalvular leakage after TAVI will negatively affect the prognosis especially when TAVI moves toward to treating patients at a young age.

Renin-angiotensin system inhibitors (RASi) are widely utilized in the area of cardiovascular disease including heart failure, myocardial infarction, and so on due to the ability to reversing the left ventricular remodeling [6, 7]. Candesartan was documented to be associated with positive improvement in left ventricular remodeling in patients with preserved left ventricular ejection fraction (LVEF) after SAVR in a randomized controlled trial [8]. Similarly, several retrospective studies also demonstrated RASi could reduce the occurrence rate of heart failure re-admission and mortality in patients with aortic stenosis after SAVR and TAVI [9–11]. However, no recommendation regarding the prescription of RASi after TAVI was proposed yet due to lacking randomized controlled trials.

Therefore, we designed this randomized controlled trial (http://www.chictr.org.cn ChiCTR2100042266) to explore the effect of adding fosinopril to standard care in patients with preserved LVEF following successful TAVI procedure on the left ventricular remodeling and fibrosis as evaluated by cardiac magnetic resonance (CMR) and echocardiography.

### Objectives {7}

The primary objective of this trial is to investigate the efficacy of RASi in the improvement of left ventricular remodeling quantified by CMR in patients after TAVI. The secondary objective is to assess potential improvements in clinical outcomes including all-cause mortality, cardiac-cause mortality, heart failure status assessed by the New York Heart Association (NYHA) class, and 6-min walk test (6MWT), and quality of life as assessed by the Kansas City Cardiomyopathy Questionnaire (KCCQ) score.

### Trial design {8}

This study will be a prospective, randomized, open-label blinded endpoint control trial in symptomatic patients with severe AS. This study protocol was approved by the institutional ethics committee of West China Hospital of Sichuan University and the local medical ethics committee of each participating center.

## Methods: participants, interventions, and outcomes

### Study setting {9}

This trial will take place at seven academic medical centers across China. The list of the involved hospitals is presented in supplemental table 1.

### Eligibility criteria {10}

Symptomatic patients with severe AS after the TAVI procedure will be randomized to receive either conventional treatment or conventional treatment plus fosinopril. Severe AS is determined according to echocardiography measures: (1) aortic valve area ≤ 1.0 cm^2^ or aortic valvular area index ≤ 0.6 cm^2^/m^2^ and (2) peak aortic jet velocity ≥ 4 m/s or mean transaortic valvular pressure gradient ≥ 40 mmHg.

#### Inclusion criteria

Subjects need to meet all the following inclusion criteria to participate in the study: (1) men or women aged ≥ 60 years, (2) presenting with symptomatic severe AS, (3) have undergone TAVI successfully which have to be approved by the local heart team according to the Valve Academic Research Consortium-2 consensus document [12], (4) heart failure is classified as function capacity level I according to the NYHA, (5) LVEF ≥ 40% assessed by echocardiography, and (6) being able to understand and provide written informed consent.

#### Exclusion criteria

Subjects presenting any of the following exclusion criteria will be excluded from the study: (1) concomitant with other significant valvular heart disease needs intervention; (2) contraindication or intolerance for the use of fosinopril including a history of angioneurotic edema, hypotension (defined as systolic blood pressure < 100 mmHg or diastolic blood pressure < 60 mmHg), estimated glomerular filtration rate < 30 mL/min/1.73 m^2^, and random serum potassium > 5.4 mmol/L; (3) life expectancy < 1 year; (4) contraindication to CMR, f.e., implantation of cardiac resynchronization therapy devices that are non-magnetic resonance conditional; and (5) prior history of myocardial infarction or dilated cardiomyopathy.

### Who will take informed consent? {26a}

Written informed consent will be collected from all participants. A researcher from the local heart team, who is trained with the study protocol will confirm the patient’s willingness to participate and eligibility criteria and obtain an informed consent.

### Additional consent provisions for collection and use of participant data and biological specimens {26b}

Not applicable

### Interventions

#### Explanation for the choice of comparators {6b}

Patients allocated in the control group will receive standard care according to the current practice.

#### Intervention description {11a}

Patients allocated in the intervention group will receive an additional use of fosinopril with an initial dose of 10 mg once daily. If the patient is well-tolerated, they will be titrated to a maximum dose of 40 mg once daily. Titration of fosinopril will be performed at the 1-month follow-up visit and afterward.

#### Criteria for discontinuing or modifying allocated interventions {11b}

Participants are allowed to discontinue and end their participation in the trial at any time for any reason. Researchers can decide to withdraw a participant from the trial at any time when encountering emergency circumstances and/or for any urgent medical reasons.

#### Strategies to improve adherence to interventions {11c}

A standard operating procedure was created for the administration of treatment of intervention and control group. Research assistants will help educate the patients. Adherence to the use of fosinopril will be assessed during follow-up visits.

#### Relevant concomitant care permitted or prohibited during the trial {11d}

In the case of patients allocated in the control group and who need to be treated for hypertension, the local Heart Team will make the decision without prescribing any RASi.

#### Provisions for post-trial care {30}

We expect that intervention-related severe adverse events in this trial will be unlikely because the use of RASi in patients with heart failure is a routine regimen in current practice. Nevertheless, we plan to provide health care at each study site for participants who may encounter trial procedure-related medical situations that need ancillary care. Post-trial care will not be provided.

#### Outcomes {12}

The primary outcome of this trial is the changes in LV mass index. The secondary outcomes include the following: (1) changes in LVEF; (2) all-cause mortality; (3) cardiac death; (4) re-admission rate due to heart failure; (5) changes in serum N terminal pro B type natriuretic peptide (NT-ProBNP), a diagnostic biomarker for heart failure; (6) NYHA class, KCCQ scores, and results of 6MWT at 24 months follow-up; and (7) changes in NYHA class, KCCQ scores, and results of 6MWT.

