### Data collection and management

#### Plans for assessment and collection of outcomes {18a}

Severe AS patients who underwent TAVI will be approached and consented for screening for eligibility. Screening evaluations include brief physical examinations, blood laboratory tests, and reviewing of medical history. Heart failure-related symptoms will be assessed for an NYHA functional classification. Transthoracic echocardiography will be conducted to assess cardiac function.

The following information will be collected during baseline evaluations: (1) demographics including date of birth, gender; (2) physical examinations including body weight, body height, resting pulse, and blood pressure; (3) any major previous health problems and use of medication by reviewing health records; (4) NYHA function capacity class by examining related symptoms; (5) results of laboratory tests including full blood count, blood lipids, glucose, liver function, renal function, and NT-ProBNP; (6) KCCQ score and results of 6MWT. Follow-up visits will take place 30 days, 3 months, 6 months, 12 months, and 24 months from randomization. At each follow-up visit, patients will be asked for any specific symptoms, any changes in the use of medication, and any adverse events. A brief physical examination will be performed to measure the resting pulse and blood pressure. Blood samples will be taken for the laboratory tests including NT-ProBNP. Transthoracic echocardiography will be performed to evaluate LV function. Moreover, NYHA function capacity class, KCCQ, and 6MWT will be evaluated. CMR scanning will be performed at baseline and be repeated at the 24-month follow-up visit to assess LV volume, mass, and function. CMR images will be analyzed independently by a central imaging core lab (West China Hospital Radiology Medicine lab). All endpoints will be adjudicated by an independent clinical events committee blinded for group allocation.

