## Statistical methods

### Statistical methods for primary and secondary outcomes {20a}

The primary and secondary endpoints will be analyzed according to the intention-to-treat principle. To compare the primary endpoint, adjusted mean difference in changes in LV mass index at 24-month follow-up visit between the two groups will be tested using linear regression with adjustment for baseline values. Time-to-event comparison (f.e., secondary endpoints including all-cause mortality and cardiac death) between the groups will be conducted using log-rank test and proportional hazards regression. A two-sided p value of 0.05 will be considered statistically significant.

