### Methods in analysis to handle protocol non-adherence and any statistical methods to handle missing data {20c}

All efforts will be made to complete the follow-up and data collection and avoid missing data. Analyses will be conducted in complete cases. We will also perform sensitivity analyses by imputing the missing data to worst cases.

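### KCCQ and 6MWT are each defined as two secondary outcomes (24-month value and undated change) and limited to complete cases; one baseline-adjusted 24-month outcome per measure would be cleaner and more precise (minor)

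*Protocol article*

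**What the plan says.** Under Outcomes {12}, the last two secondary items are "6) NYHA class, KCCQ scores, and results of 6MWT at 24 months follow-up; and (7) changes in NYHA class", with KCCQ and 6MWT following NYHA in item (7) as they do in item (6). Item (6) is dated at 24 months; item (7) is not dated.

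The section on statistical methods for primary and secondary outcomes {20a} names two analyses. The 24-month change in LV mass index "will be tested using linear regression with adjustment for baseline values". For events: "Time-to-event comparison (f.e., secondary endpoints including all-cause mortality and cardiac death) between the groups will be conducted using log-rank test and proportional hazards regression". No method is named for NYHA, KCCQ or 6MWT. The only threshold is: "A two-sided p value of 0.05 will be considered statistically significant".

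On missing data {20c}: "Analyses will be conducted in complete cases", with worst-case imputation as a sensitivity analysis.

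Two further facts matter. The inclusion criteria require that "heart failure is classified as function capacity level I according to the NYHA". The data-collection section {18a} states: "Follow-up visits will take place 30 days, 3 months, 6 months, 12 months, and 24 months from randomization". That section and Table 1 have KCCQ and 6MWT measured at baseline and at all five of these visits.

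**The concern.** A 24-month score and a change score ask the same question about treatment. Listing them as separate outcomes is harmless only if they are analysed so that they agree. If they are analysed without baseline adjustment they can disagree. There are then two chances of a nominally significant result for one measure, and a choice of which to report. That choice is unwelcome in an open-label trial, where patients know their allocation and KCCQ is completed by the patient. The missing date on item (7) leaves further room.

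Precision is also at stake. Baseline KCCQ and 6MWT are collected in any case, and using them as covariates narrows the confidence interval. Under the complete-case rule, a patient followed to month 12 who misses month 24 is lost from item (6) despite four earlier follow-up measurements.

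**Working it through.** **The plan's own figure.** The only power statement concerns the primary endpoint: more than 90% with 100 per group, difference 20 g/m², SD 35 g/m², 10% dropout. With 90 evaluable per arm, SE = 35 × √(2/90) = 5.22; 20/5.22 − 1.96 = 1.87; power = 96.9%. The statement holds. No power or error rate is given for KCCQ, 6MWT or NYHA.

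**Inputs.** Two-sided alpha 0.05 {20a}; two definitions per measure {12}; NYHA class I at entry (inclusion criteria). The correlation ρ between baseline and 24 months is not in the article; I assume 0.3 to 0.8. I also assume equal variances at the two times.

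**Variances.** With X the baseline value, Y the 24-month value and variance 1:
- raw 24-month value: 1
- change Y − X: 2(1 − ρ)
- baseline-adjusted: 1 − ρ²

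**Two unadjusted tests.** Cov(Y, Y − X) = 1 − ρ, so the two test statistics correlate at (1 − ρ)/√(2(1 − ρ)) = √((1 − ρ)/2). The chance that at least one exceeds 1.96 in absolute value under no effect comes from the bivariate normal distribution.

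| ρ (assumed) | Correlation of the two tests | Chance of at least one false positive | Adjusted variance ÷ raw 24-month | Adjusted variance ÷ change |
|---|---|---|---|---|
| 0.3 | 0.592 | 8.8% | 0.91 | 0.91/1.40 = 0.65 |
| 0.5 | 0.500 | 9.1% | 0.75 | 0.75/1.00 = 0.75 |
| 0.7 | 0.387 | 9.4% | 0.51 | 0.51/0.60 = 0.85 |
| 0.8 | 0.316 | 9.5% | 0.36 | 0.36/0.40 = 0.90 |

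At ρ = 0.5, adjustment is worth 1/0.75 = 1.33, or about 33% more patients, against either unadjusted form.

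**Both forms adjusted.** If Y − X = a + b·treatment + c·X, then Y = a + b·treatment + (c + 1)·X. The treatment effect b is the same. In a simulated data set both regressions gave p = 0.0163. There is then no inflation and no loss, and the second listing is redundant.

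**NYHA.** Baseline is 1 for everyone, so change = 24-month class − 1. Subtracting a constant leaves any two-group test unchanged; in simulated data the t-test and the Mann-Whitney test each gave the same p value for value and change. NYHA adds no false positives, and baseline adjustment gains nothing.

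**Extra visits.** With complete data, a mixed model with baseline and treatment each crossed with visit and an unstructured covariance gives the same 24-month contrast as the baseline-adjusted analysis of month 24 alone. The extra visits help only where month 24 is missing. The article's own sizing allows 10% dropout, that is 0.10 × 200 = 20 patients.

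**The case against.** The strongest objection is that the criticised analysis is not in the article. No test, adjusted or unadjusted, is named for these measures. A separate statistical plan is mentioned but not shown, and the model for secondary outcomes and any multiplicity rule are commonly left to it. If the analysts carry over the approach set for the primary endpoint, the two versions of each measure give one result. This stands, and it is why the 9% figure is conditional.

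A reader might infer that all three measures will each be tested twice, with a chance of at least one false positive of 1 − (1 − 0.0907)³ = 24.8%, or 1 − 0.95¹¹ = 43% over 11 secondary comparisons. The documents do not support this. NYHA value and change are the same test. Counting NYHA once at ρ = 0.5 gives 1 − 0.95 × (1 − 0.0907)² = 21.5%, against 1 − 0.95³ = 14.3% with one test each, and both still assume independence between related measures. The 43% also treats correlated pairs as independent, and cardiac death is contained in all-cause death.

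A reader might also infer that only month 24 is used, so that earlier visits count for nothing. That is not established: item (7) is undated and could refer to other visits.

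What remains rests on what is written: two definitions of one measure, one of them undated, and an explicit complete-case rule. Endpoint definitions are the protocol's business, and the article states the missing-data rule itself.

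**Conclusion.** The point holds as a minor one on secondary outcomes. Items (6) and (7) overlap for KCCQ and 6MWT, coincide for NYHA if the change is taken at month 24, and leave the time point of the change open. If KCCQ or 6MWT is tested unadjusted in both forms, the false-positive chance for that measure is 8.8% to 9.5% instead of 5%, and precision is lost by the ratios tabulated above. These sizes rest on an assumed ρ and on equal variances at the two times; whether they arise depends on an analysis that the article does not specify. For KCCQ and 6MWT the complete-case rule discards usable visits for patients who miss month 24. The primary endpoint is single, and its type I error is unaffected.

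**What to change.** - Merge items (6) and (7) into one outcome per measure. For KCCQ and 6MWT: the baseline-adjusted treatment difference at 24 months. List NYHA once, without expecting a gain from baseline adjustment.
- Replace the complete-case analysis of KCCQ and 6MWT with a mixed model for repeated measures over the five scheduled visits (baseline, visit, treatment, treatment-by-visit, baseline-by-visit), reporting the 24-month contrast. A patient who misses month 24 then still contributes.
- State that this relies on data being missing at random, and keep the worst-case imputation as the sensitivity analysis. Deaths before month 24 are not missed visits in this sense and need their own stated rule.

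The cost is a change of wording and standard software. No new data or visits are needed, and there are fewer p values to report.

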#### Participant timeline {13}

The workflow is depicted in the flowchart (Fig. 1); schedule of enrollment, intervention, and examinations are presented in Table 1.

**Fig. 1 Fig1:**
[figure not shown]
Flowchart of the study design

**Table 1 Tab1:** Schedule of enrollment, interventions, and examinations

Time point	Study period						
	Enrolment	Allocation	Post-allocation				
	1 week pre	0	1 month	3 months	6 months	12 months	24 months
Enrollment							
Eligibility screen	X						
Informed consent	X						
Allocation		X					
Interventions							
Standard care			X	X	X	X	X
Standard care plus fosinopril			X	X	X	X	X
Assessments							
Demographics	X						
Physical examinations	X		X	X	X	X	X
Medical history	X		X	X	X	X	X
Laboratory tests	X		X	X	X	X	X
NYHA class	X		X	X	X	X	X
Transthoracic echocardiography	X		X	X	X	X	X
CMR		X					X
KCCQ		X	X	X	X	X	X
6-min walk test		X	X	X	X	X	X
Adverse events			X	X	X	X	X

*NYHA* New York Heart Association, *CMR* cardiac magnetic resonance, *KCCQ* Kansas City Cardiomyopathy Questionnaire

#### Sample size {14}

The sample size is calculated based on the primary endpoint, namely the difference in changes of LV mass index at 24 months between the intervention group and the control group. Prior prospective studies reported a difference of 10 g/m^2^ and 18 g/m^2^ in absolute changes in LV mass index at 6 months and at 12 months, respectively, comparing with and without RASi treatment [8, 13]. A sample size of 100 per group will have more than 90% power to detect an expected difference of 20 g/m^2^ at an alpha level of 0.05, given a standard deviation of 35 g/m^2^ and a dropout rate of 10%.

#### Recruitment {15}

Patients undergoing TAVI from seven academic medical centers across China will be screened for eligibility and recruited about 1 week after the TAVI procedure.

### Assignment of interventions: allocation

#### Sequence generation {16a}

Eligible patients will be randomized in a 1:1 ratio to receive standard care or standard care plus fosinopril. Centralized random allocation will be performed after receipt of informed consent using a block size of 4 without stratification. Allocation sequence was generated using R with the package randomizeR prior to study initiation.

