#### Concealment mechanism {16b}

Generated allocation sequence is to be concealed in opaque, sealed envelopes that are consecutively numbered. An independent research assistant is responsible for keeping these envelopes unopened and allocated.

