#### Implementation {16c}

The allocation sequence will be generated by a statistician. Participants who are eligible for this trial and willing to give written consent will be enrolled by a trial researcher. The research assistant will directly inform the clinician about the group allocation.

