### Assignment of interventions: blinding

#### Who will be blinded {17a}

Due to logistic reasons, it will not be feasible to blind the natural course of this study to patients nor clinicians. However, all endpoints will be adjudicated by an independent imaging core lab or the clinical event committee, who are blinded to the group allocation.

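### One fixed, published block size of 4 without centre stratification, in an open-label seven-hospital trial that does not say where its envelopes are held: a weak allocation method that is cheap to improve before recruitment

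*Protocol article*

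**What the plan says.** Under Sequence generation {16a}: "Eligible patients will be randomized in a 1:1 ratio to receive standard care or standard care plus fosinopril", followed by "Centralized random allocation will be performed after receipt of informed consent using a block size of 4 without stratification". Under Concealment mechanism {16b}: "Generated allocation sequence is to be concealed in opaque, sealed envelopes that are consecutively numbered" and "An independent research assistant is responsible for keeping these envelopes unopened and allocated". Implementation {16c} adds: "The research assistant will directly inform the clinician about the group allocation".

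On blinding, section {17a} concedes that "it will not be feasible to blind the natural course of this study to patients nor clinicians"; endpoint assessment is blinded. Study setting {9} says: "This trial will take place at seven academic medical centers across China". According to section {26a}, a researcher from the local heart team confirms eligibility and obtains consent.

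For the primary endpoint, section {20a} says that the difference in change in LV mass index "will be tested using linear regression with adjustment for baseline values". Centre is not named. The cardiovascular magnetic resonance protocol has images acquired on each site's own 1.5-T scanner, and section {18a} has them read by one core lab.

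**The concern.** Three stated choices interact.

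- **Predictability.** The block size is fixed and public, and past allocations are known to those who treat. A recruiter who can see a run of allocations within a block can work out the later ones. Randomising only after consent does not remove this risk, because an expected allocation can still influence whom the recruiter approaches or judges eligible. Blinded endpoint reading does not protect against selection at that step.
- **Balance.** A single unstratified list balances the arms over the whole trial, not within a hospital. Scanners and local standard care can differ between hospitals.
- **Precision.** If change in LV mass index differs between hospitals, a model without centre leaves that variation in the error term.

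The article does not say whether the envelopes are one centrally held series or are distributed to the hospitals. That decides which of the first two problems applies.

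**Working it through.** **Inputs from the article.** Allocation 1:1, block size 4, seven centres, 100 per group, dropout 10% (90 evaluable per group), difference 20 g/m², SD 35 g/m², two-sided alpha 0.05. **Assumptions.** Equal expected recruitment per centre (200/7 ≈ 29); a between-centre share of variance of 5% to 20%. The article gives neither.

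**1. The plan's own figure.** Standard error = 35 × √(2/90) = 5.22. Then 20/5.22 = 3.83, and 3.83 − 1.96 = 1.87, so power = Φ(1.87) ≈ 96.9%. The claim of more than 90% is correct and is not in dispute.

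**2. Envelopes at sites in whole blocks.** There are six equally likely sequences: AABB, ABAB, ABBA and their mirror images.

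- Certain allocations: 2 in AABB, 1 in ABAB, 1 in ABBA. Mean 4/3 per block, and (4/3)/4 = 33.3%.
- Best guess (the arm with more places left; a coin toss when equal): AABB 0.5 + 0 + 1 + 1 = 2.5; ABAB 0.5 + 1 + 0.5 + 1 = 3; ABBA 0.5 + 1 + 0.5 + 1 = 3. Mean 8.5/3 = 2.83, and 2.83/4 = 70.8%, against 50% by chance.
- Within a hospital the arms can then differ by at most 2.
- A larger block helps little if it is fixed and known: size 6 gives 25.0% certain and 68.3% guessed; size 8 gives 20.0% and 66.6%.

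**3. One central list shared by seven hospitals.** Simulation of 50 blocks of 4, each patient falling at random in one of seven equal centres (20,000 trials):

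- A clinician who sees only local allocations and guesses the opposite of the last one is right about 53% of the time. If the site also knows its envelope numbers, and so its positions in the block, the figure is still about 53% at a one-seventh share of recruitment, 56% at 30% and 60% at 50%.
- Mean arm difference within a centre: about 3.9 patients.
- Largest arm difference in any centre: median 8 (5th to 95th percentile 4 to 13).
- Chance that some centre differs by 10 or more: 31%.

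**4. Centre in the model.** If a share *r* of the variance lies between centres, adjustment reduces the SD to about 35 × √(1 − *r*).

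| *r* (assumed) | SD | Power at 20 g/m², 90 per group |
|---|---|---|
| 0 | 35.0 | 96.9% |
| 0.05 | 34.1 | 97.6% |
| 0.10 | 33.2 | 98.1% |
| 0.20 | 31.3 | 99.0% |

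The six degrees of freedom spent on centre, with about 180 evaluable patients, change these figures by less than 0.1 point.

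**The case against.** The strongest reply is that the design as written is sound. The article describes central allocation after consent, one consecutive series and a single independent assistant who reports the result. Nothing in it sends envelopes to hospitals. On that reading a site guesses barely better than chance, and where the envelopes are stored is a detail for the full protocol. This largely stands. A reader might infer that central allocation and numbered envelopes contradict each other; they do not if one person holds one series centrally. What remains is that the article does not say so, although the risk turns on it.

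A reader might also add the two harms together. That is not supported: 71% guessing requires blocks to run within a hospital, which limits imbalance there to 2, whereas a worst-centre difference near 8 requires the shared list.

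On centre, an analysis without it is valid after unstratified randomisation, because the standard error already reflects chance imbalance. It would be wrong to call the comparison confounded. The endpoint is change within a patient, adjusted for baseline and read in one core lab, so constant scanner offsets should largely cancel if patients are rescanned at the same site. The analysis plan, not shown here, may also include centre. All of this stands and limits the centre argument to precision. It does not argue for keeping a fixed, disclosed block size without stratification.

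**Conclusion.** The point holds as a worthwhile improvement. The article fixes a weaker allocation method than an open-label multicentre trial needs, and leaves unstated the one fact that decides how it is weak. Either allocation is predictable (33% certain, 71% guessable, if whole blocks go to hospitals), or it is close to unpredictable for a site of average size (about 53%) and blocking does nothing for balance within hospitals (median worst-centre difference 8, and a 31% chance of 10 or more). The second reading is the more natural one. The balance figures assume equal centres, and the site-level guessing figure rises with a site's share of recruitment.

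The gain from adding centre is small: power of about 97% rises to between 97.6% and 99.0% if 5% to 20% of the variance lies between centres, a range that is assumed. A reader might infer that the sample size or the validity of the primary test is threatened. Neither is: the stated power reproduces, and the test remains valid without centre.

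**What to change.** Before the first patient:

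1. Regenerate the list with permuted blocks of randomly varying size (4 and 6, for example), stratified by centre. Keep the sizes actually used in a restricted document. The two changes belong together: stratifying makes blocks run within hospitals, where a fixed, published size would be at its most predictable.
2. Release each allocation centrally, only after the patient's enrolment has been logged; the web-based data system already planned can record this. State in sections {16a} to {16c} that any envelopes are a centrally held backup.
3. Add centre as a factor in the primary regression, alongside the baseline value.

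The cost is a new list from the R code already in use, minor set-up work and six degrees of freedom. The Trial status section places the start of recruitment after publication of the article, so no patient need be affected. Concealment cannot be repaired once patients are enrolled.
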